## **7.7 Data collection**

In hospitals in England and Wales, nearly all data described below are already collected for NELA as part of routine care, under section 251 of the NHS Act 2006. NELA data are entered on to the secure online web portal locally by the range of clinicians caring for laparotomy patients, with each specialty entering data on their area of clinical care. Existing NELA leads at each hospital monitor data completeness, addressing any missing data and taking responsibility for completing and locking patient records. Data completeness is monitored routinely by the central NELA team and fed back to sites regularly as an audit standard. A small number of data fields will be added to the NELA web portal for FLO-ELA, only becoming activated for those patients who have given consent (or alternatives for those lacking capacity) and been randomised. Clinicians will be asked to complete these data fields prospectively, as they currently do for NELA. Research nurses will check for data completeness and accuracy of the FLO-ELA specific data fields after the intervention period. This will be monitored and actively managed throughout the trial. As NELA is not commissioned in Scotland and Northern Ireland, an eCRF database will be produced with identical NELA data fields to those used in FLO-ELA. Data entry to a secure online portal will be carried out by local research teams. This database will issue an eCRF ID in the same format to the NELA ID. Local investigators in all nations will also enter identifiable data onto the secure online randomisation system, to allow linkage to national databases.

HQIP are the data controller for NELA (hospitals in England and Wales) and a data sharing agreement is in place allowing sharing of pseudonymised NELA data for FLO-ELA participants as described in the participant consent materials. The FLO-ELA trial Sponsor is the data controller for the FLO-ELA data fields within the NELA database, for the data within the eCRF database used in Scotland and Northern Ireland, and for the data held within the randomisation system. FLO-ELA participant identifiable data held in the trial randomisation system will be linked to national databases to obtain outcome data including mortality and hospital (re)admission. Outcomes data will be merged with pseudonymised NELA/eCRF data to allow statistical and health economic analyses. Data sharing agreements will be established with NHS Digital and devolved nation equivalents.

### **7.7.1 Randomisation data**

- NHS (England), CHI (Scotland) or H&S (Northern Ireland) number\*
- Date of birth\*
- Gender\*

- Postcode\*
- NELA ID (or assigned eCRF ID in Scotland and Northern Ireland)
- Checklist to ensure the patient meets the eligibility criteria
- Patient age
- ASA score
- Indication for planned surgery
- Centre ID (collected automatically during log-in to randomisation system)

\*patient identifiers are collected to allow follow up of all randomised patients. See: section 7.10.

### 7.7.2 NELA dataset

The full list of data collected by NELA is in the NELA Participant Manual available at <http://nela.org.uk/Audit-info-Documents#pt>. The full data field list and subset of data fields that are shared with FLO-ELA (mirrored in the eCRF used in Scotland/Northern Ireland) are shown in Appendix 2.

*Peri-operative data* include: Date of birth, gender, date/time of hospital admission and other key aspects of pre-operative care, urgency and indication for surgery, patient risk scores and physiology markers, seniority of surgeon and anaesthetist during surgery, operative findings and procedure performed

*Outcomes data* include: Duration of stay in level 3 or level 2 bed, vital status at discharge.

### 7.7.3 Supplementary data fields for FLO-ELA

#### **Intervention patients:**

##### *Intra-operative:*

- Cardiac output monitoring (COM): time started / monitor type
- Number of cycles through protocol (number of COM-guided fluid boluses given)
- Total volume of crystalloid, colloid, blood and blood product administered
- Inotrope/vasopressor administered – type and mode of administration (bolus / infusion)

##### *During the six hours after surgery:*

- Cardiac output monitoring (COM): time started and stopped / monitor type
- Number of cycles through protocol (number of COM-guided fluid boluses given)
- Total volume of crystalloid, colloid, blood and blood product administered
- Inotrope/vasopressor administered – type and mode of administration (bolus / infusion)
- Duration of trial intervention (if <6 hours, reason for early termination: transfer to level 1 care area / other)

#### **Control group patients:**

*Intra-operative:*

- Total volume of crystalloid, colloid, blood and blood product administered
- Inotrope/vasopressor administered – type and mode of administration (bolus / infusion)
- Cardiac output monitoring used in a control patient? If yes: time started and indication (patient deterioration / other reason)

*During the six hours after surgery:*

- Total volume of crystalloid, colloid, blood and blood product administered
- Inotrope/vasopressor administered – type and mode of administration (bolus / infusion)
- Cardiac output monitoring used in a control patient? If yes: time started and indication (patient deterioration / other reason)
- Duration of trial intervention (if <6 hours, reason for early termination: transfer to level 1 care area / other)

**7.7.4 Outcomes data from NHS Digital or devolved nation NHS datasets**

- Mortality at 90 days and one year (via the ONS/NSSISD)
- Duration of the index hospital admission (HES/NSSISD/PEDW)
- Readmission to hospital as an inpatient (overnight stay) within 90 days and within one year of randomisation (HES/NSSISD/PEDW)

**7.8 Predefined protocol deviations**

- Failure to use cardiac output monitoring in an intervention group patient
- Failure to follow the haemodynamic algorithm (defined as at least one cycle of fluid bolus with measurement of stroke volume response) in an intervention group patient when a cardiac output monitor is being used.
- Use of cardiac output monitoring in a control group patient, including forms of monitoring based on stroke volume variation or pulse pressure variation only.

**7.9 Follow-up procedures**

Local investigators will review a participant's medical record (paper or electronic) in order to check and complete NELA/eCRF data entry. To collect data on the primary and secondary outcomes and enable the health economic analysis, we will request hospital episode statistics and mortality data from NHS Digital and equivalent devolved nation organisations. Prospective consent for data linkage will be sought before enrolment into the trial.

### 7.10 Withdrawal of participants

All study participants are free to withdraw from the study at any time. A participant withdrawal form will be completed for all participants withdrawn from the trial. However, ONS/HES (or equivalent) data will still be collected for these patients, and they will be included in the final analysis on an intention to treat basis, unless a participant specifically asks for their data not to be included (see section 8). In a small number of cases, after a patient has been randomised the patient may not ultimately undergo a surgical procedure in line with NELA inclusion criteria. This may be due to a change in clinical condition before the start of surgery such that no surgery is performed, due to a change in the surgery performed or due to unexpected findings during surgery. These patients are currently not included in the NELA dataset, and any data already entered to NELA is removed. Of these patients:

- Patients who do not ultimately undergo surgery will **not** be included in the analysis (see Section 5.9 on estimand framework). A trial withdrawal form should be completed for these patients.
- Patients who do undergo surgery **will** be included in the analysis, as long as they were *expected* to undergo an eligible NELA procedure at the time of randomisation. If it is thought to be clinically appropriate by the attending clinicians, trial treatment should continue in accordance with allocated group.

### 7.11 End of study definition

The end of the study is defined as the point when the last patient has completed one year follow-up. The Data Monitoring and Ethics Committee (DMEC) will monitor safety data throughout the trial. Based on these results, they could recommend termination of the trial on safety grounds. They will report any concerns to the Trial Steering Committee (TSC), who will inform the Sponsor and take appropriate action, which may include stopping the trial, to address concerns about participant safety. The Research Ethics Committee will be informed in writing if the trial is suspended or terminated early.

### 7.12 Schedule of assessment

| Event/Visit                                                           | Screening | Pre-op | Intra-op | 24 hrs post-op | Hospital discharge | Post-op day 90 | Post-op 365 days |
|-----------------------------------------------------------------------|-----------|--------|----------|----------------|--------------------|----------------|------------------|
| Inclusion/exclusion criteria                                          | x         |        |          |                |                    |                |                  |
| Informed consent                                                      | x         |        |          |                |                    |                |                  |
| NELA/eCRF pre-operative data*                                  |           | x      |          |                |                    |                |                  |
| Randomisation                                                         |           | x      |          |                |                    |                |                  |
| NELA/eCRF intraoperative data*                                 |           |        | x        | x              |                    |                |                  |
| Fluid and inotropic therapy                                           |           |        | x        | x              |                    |                |                  |
| NELA/eCRF postoperative data by medical notes review*          |           |        |          | x              | x                  |                |                  |
| NELA/eCRF duration of hospital stay and days in critical care* |           |        |          |                | x                  |                |                  |

|                             |  |  |  |   |   |   |   |
|-----------------------------|--|--|--|---|---|---|---|
| SAE                         |  |  |  | x | x | x | x |
| Hospital readmissions (HES) |  |  |  |   |   | x | X |
| Vital status (ONS)          |  |  |  |   |   | x | x |
| End of trial form           |  |  |  |   |   |   | x |

***\*these data are already collected as routine care by medical teams for NELA in England and Wales***

## **8 STATISTICAL CONSIDERATIONS**

### **8.1 Sample size calculation**

The original sample size calculation was based on the original primary outcome of mortality within 90 days of randomisation. Based on a 5% alpha level, 90% power, and assuming a 2% dropout rate and a 19% 90-day mortality rate in the usual care arm, 3823 patients were required in each arm (7646 total) to detect a risk ratio of 0.85 (equivalent to an absolute decrease from 19% to 16.15%) for the primary outcome.

For the new primary outcome of DAOH-90, we calculated that 3138 participants (1569 per group) would be required to detect a 3.2-day increase in DAOH-90 (from mean 64.5 (SD 28.0) days in the control group to 67.7 (SD 27.1) days in the intervention group), with 90% power, a 5% alpha (Type I error) level, and a 2% dropout rate.

The revised sample size calculation was made without access to or knowledge of unblinded data. The parameter choices for this sample size calculation were derived from simulation as detailed in the trial Statistical Analysis Plan V4.0. In summary:

#### ***Mortality***

Patients who died within 90 days are assigned a DAOH-90 value of 0 (18). Prior to the revised sample size calculation based on the DAOH-90 primary outcome, pooled (control and intervention group combined) 90-day mortality was reviewed on the advice of the FLO-ELA Data Monitoring Committee in September 2019 and found to be ~12%. Therefore, the assumed control-arm event was set at ~13%, and as per the original sample size calculation, we assumed the intervention decreased mortality by 15% (relative risk 0.85) to ~11%.

#### ***Time spent in hospital***

Previous studies of this intervention in higher risk (mortality >10% at longest follow-up) patient populations have found reductions in postoperative length of stay (LoS) of 1.3 days (95% CI 0.1-2.5) (6,12–15,26–28). When also considering morbidity-related hospital readmissions, a mean 2-day difference in time spent in hospital for those surviving to 90-days is realistic.

#### ***Overall effect on DAOH-90***

Using statistical simulation based on the above parameters and summary hospital length of stay data from NELA (November 2020), we estimated that a 2-day difference in time in hospital for survivors and a relative risk reduction for 90-day mortality in patients in the intervention arm of 0.85 would give expected mean [SD] DAOH-90 in the Control arm of ~ 64.5 days [28.0] and in the intervention arm ~ 67.7 days [27.1], i.e. an overall 3.2-day increase in DAOH-90 in the intervention group.

This proposed effect size is realistic and of clear impact to patients and healthcare systems, representing several hundred lives saved each year, and a mean of two days less time spent in hospital for survivors if the intervention is effective and fully implemented.

## **8.2 Statistical analysis**

The number of patients recruited and followed up will be recorded in a CONSORT flow chart. Baseline characteristics will be summarised by treatment group.

Patients will be analysed according to the treatment group to which they were randomised and all eligible patients for whom an outcome is available will be included in the analysis (29) except (i) those randomised in error (i.e. were ineligible at the time of randomisation) and (ii) those who were eligible and randomised but did not ultimately undergo surgery as per the principal stratum strategy outlined in Table 1. The former exclusion (participants randomised in error) is based on pre-randomisation information (i.e. failure to meet the eligibility criteria) and as such will be unbiased. The latter exclusion (participants who did not undergo surgery) will be unbiased for the principal stratum effect under the assumption that treatment group allocation does not affect whether participants undergo surgery or not (i.e. a participant in the intervention group who does not undergo surgery would also not receive surgery had they been allocated to the control, and *vice versa*). This assumption is justified on the basis that, in most cases, the relevant decision makers will be unaware of trial group allocation until surgery starts (i.e. at the point the decision is made). Further, the decision not to proceed with surgery has large health implications for the patient, and is only undertaken in response to a major change in the patient's clinical condition since surgery was initially planned, and it is implausible that such a fundamental change in patient care would be undertaken on the basis of the planned method of fluid delivery.

For each analysis we will present the number of patients included in the analysis, a summary measure of the outcome in each treatment group, treatment effect, 95% confidence interval and a two-sided p-value. P-values <0.05 will be considered statistically significant.

The estimand for the primary outcome (days alive and out of hospital within 90 days of randomisation) will be estimated using a mixed-effects linear regression model, with a random-intercept for centre (30). The model will be adjusted for the minimisation factors of patient age and ASA class (I, II, III, IV, and V) (31), as well as the following prognostic baseline covariates: urgency of surgery (Immediate, Urgent, and Expedited), Glasgow Coma Score (GCS), systolic blood pressure and pulse rate (32). Urgency of surgery and ASA class will be included as categorical variables, while patient age, GCS, systolic blood pressure, and pulse rate will be included as continuous variables. Patient age and GCS will be including assuming FLO-ELA protocol v5.0

a linear association with the outcome, and systolic blood pressure and pulse rate will be included using restricted cubic splines with 3 knots (knots will be placed based on Harrell's recommended percentiles) (33,34). Missing baseline data will be handled using mean imputation for continuous variables, and a missing indicator variable for categorical variables (35). The estimands for the secondary outcomes will be estimated using an analogous mixed effects logistic regression model, with covariates and random effect specification as above and the same principal stratum strategy adopted.

We will also conduct subgroup analysis of the primary outcome by urgency of surgery (Immediate vs. Urgent vs. Expedited), age (<70 vs. 70+), indication for surgery (bowel perforation vs. bowel obstruction without perforation vs. other indications), gender (male vs. female) and a pre-operative predicted risk score, which will be determined, with a binary cut-off established for the subgroup analysis, before any of the data is viewed. In addition, we will carry out two analyses to assess the impact of the Covid-19 pandemic on treatment effect; the first will be a subgroup analysis based on whether patient was randomised pre or post Covid-19 pandemic (pre = prior to cut-off date 30 January 2020, post = 30 January 20 or after) and in the second analysis, subgroups will be Covid-19 status of patient (negative [0] or positive [1]), subject to test availability - this information has only been recorded systematically since March 2020. Subgroup analysis will be undertaken by statistically testing the interaction between treatment group and subgroup variable. In the case of subgroup variables age and preoperative risk score, this will involve in addition the fitting of cubic splines as described in SAP V4.0. Subgroup specific estimates and 95% confidence intervals will also be reported. Any subgroup findings will be treated with caution and will be given less weight than the primary analysis.

**Days at home analysis:** The revised primary outcome, DAOH-90, may be considered a proxy for days *at home* within 90 days (DAH-90). However, we will not have sufficiently detailed data to track each individual pathway in terms of residence outside of hospital for everyone in the database.

In order to assess if inference on DAOH-90 may be extended to DAH-90, we will analyse data for a subset of FLO-ELA participants for whom post-discharge destination ("home" or "residence other than own home") is recorded. This was recorded as part of NELA audit up to December 2019, but not thereafter. DAH-90 will be calculated in the same way as DAOH-90, except that in instances where a patient is discharged to residence other than own home, DAH-90 will be set to zero. The primary analysis on DAOH-90 will be repeated with DAH-90 for patients with available data. This will be compared against results of the primary analysis on DAOH-90 for (i) all patients (ii) subset of patients on which DAH-90 analysis carried out.

The same overarching analysis strategy will be applied with respect to all sub-group analyses and for the days-at-home analysis as that described for the primary estimand.

We will in addition present summary statistics on NELA-defined treatment standards and the pre-surgical risk profile of FLO-ELA participants according to whether the patient was randomised in the pre or post Covid pandemic era, using the same cut-off date as for the treatment effect analysis, i.e. prior to (pre) or on or after (post) 30 January 2020. The cut-off date of 30th January 2020 was chosen as this was when Covid-19 was first confirmed to be present in the UK.

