| 7.7  | Status at discharge                                                                                                                                                                                 | 
 
○ Dead
 
○ Alive
 
○ Still in hospital at 60 days
 
                                                                                                                                                                                                                                                                       | ‘Still in hospital at 60 days’ option to be used when approaching an audit deadline by which all incomplete cases need to be locked                                                                                                                                                                        |
| 7.8  | Date discharged from hospital                                                                                                                                                                       | <hr/> (DD/MM/YYYY)
Date required                                                                                                                                                                                                                                                                                                                                                     | Date of discharge, NOT date fit for discharge.
Only shared with FLO-ELA for those discharged alive , to avoid generating date of death as a direct patient identifier                                                                                                                            |

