| 7.9  | Discharge destination                                                                                                                                                                               | 
 
○ Own home/sheltered housing
 
○ Residential care
 
○ Nursing care
 
○ Unknown
 
                                                                                                                                                                                                                                   | No longer collected in NELA from 1/12/2019                                                                                                                                                                                                                                                                 |

|             | COVID-19 Questions                                          |                                                                                                                                                                                                            | New Questions added in 2020 |
|-------------|--------------------------------------------------------------------|------------------------------------------------------------------------------------------------------------------------------------------------------------------------------------------------------------|-----------------------------|
| 7.10 | Please indicate the patient's SARS-CoV-2/COVID-19 infection status | 
 
○ Covid positive – confirmed pre-operatively
 
○ Covid positive – confirmed post-operatively
 
○ Covid negative throughout in-patient stay
 
 |                             |
| 7.11 | NO LONGER REQUIRED                                                 | NO LONGER REQUIRED                                                                                                                                                                                         |                             |
| 7.12 | NO LONGER REQUIRED                                                 | NO LONGER REQUIRED                                                                                                                                                                                         |                             |

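### Read literally, the days-at-home analysis leaves out patients who die in hospital, so its treatment effect comes from a set selected after randomisation on part of the outcome

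*Combined protocol and SAP*

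**What the plan says.** Section 8.2 (Days at home analysis) says "we will analyse data for a subset of FLO-ELA participants for whom post-discharge destination" is recorded, either as own home or as another residence. On availability it adds: "This was recorded as part of NELA audit up to December 2019, but not thereafter".

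The scoring rule is "DAH-90 will be calculated in the same way as DAOH-90, except that in instances where a patient is discharged to residence other than own home", in which case the value is zero. The model step is "The primary analysis on DAOH-90 will be repeated with DAH-90 for patients with available data". The result is then to be compared with DAOH-90 in two groups, listed as "i) all patients (ii) subset of patients on which DAH-90 analysis carried out". Section 8.2 also applies the same overall strategy "for the days-at-home analysis as that described for the primary estimand".

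Three other places bear on this:

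- Section 5.7 gives every participant who dies within 90 days a DAOH-90 of zero. Deaths and hospital days come from linked national data, not from the audit record.
- Appendix 2, field 7.9 (discharge destination) offers own home or sheltered housing, residential care, nursing care, or unknown. Its note reads "No longer collected in NELA from 1/12/2019".
- Appendix 2, field 7.7 (status at discharge) is where death is recorded. It also has the option "Still in hospital at 60 days", meant for records that must be locked near an audit deadline.

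**The concern.** A patient who dies in hospital has no discharge destination, and field 7.9 has no code for one. The inclusion rule in section 8.2 therefore cannot be met by such a patient, yet the scoring rule next to it gives that patient a known value of 0.

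If the inclusion rule governs, the set depends on survival to discharge. Section 8.1 assumes that treatment changes mortality, so different proportions of the two arms would be removed and randomisation would no longer protect the comparison. Section 8.2 defends its exclusion of patients who have no surgery on the ground that allocation does not affect whether surgery happens. That argument cannot be used for in-hospital death, and no other is given. The target population in Table 1 is patients who undergo surgery, not those discharged alive.

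At stake is how the DAH-90 estimate, its confidence interval and its p-value are read, and whether setting them beside the all-patient DAOH-90 result means anything.

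**Working it through.** **Inputs from section 8.1.** Mean DAOH-90 is 64.5 days (control) and 67.7 days (intervention), a difference of 3.2. Control 90-day mortality is about 13% with relative risk 0.85, so 0.13 × 0.85 = 11.05% under the intervention. The stated difference among survivors is 2 days.

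**Step 1: reproduce the plan's figure.** Deaths score 0, so survivor mean = overall mean / (1 − mortality).

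- Control: 64.5 / 0.87 = 74.14
- Intervention: 67.7 / 0.8895 = 76.11
- Difference: 1.97 days, matching the stated 2 days

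Split of the 3.2 days: hospital time gives 1.97 × (1 − 0.12025) = 1.74, where 0.12025 is the average mortality. Mortality gives 0.0195 × 75.12 = 1.46, where 75.12 is the average survivor mean. Mortality therefore carries 1.46 / 3.2 = 46% of the planned effect.

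**Step 2: drop in-hospital deaths.** Let f be the share of 90-day deaths that occur in hospital. The documents do not give f, so it is varied. Subset mean = overall mean / (1 − f × mortality).

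| f (assumed) | Dropped, control | Dropped, intervention | Mean, control | Mean, intervention | DAOH-90 effect |
|---|---|---|---|---|---|
| 0 | 0% | 0% | 64.50 | 67.70 | 3.20 |
| 50% | 6.5% | 5.53% | 68.98 | 71.66 | 2.68 |
| 70% | 9.1% | 7.74% | 70.96 | 73.38 | 2.42 |
| 90% | 11.7% | 9.95% | 73.05 | 75.18 | 2.13 |
| 100% | 13.0% | 11.05% | 74.14 | 76.11 | 1.97 |

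The subset effect is (3.20 − 2.68) / 3.20 = 16% to (3.20 − 1.97) / 3.20 = 38% smaller. Comparison (i) would show this gap before destination plays any part.

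**Step 3: comparison (ii), both outcomes in the same patients.** Let q be the share of days lost to non-home discharge (assumed), so DAH-90 mean = DAOH-90 mean × (1 − q). The DAH-90 effect minus the DAOH-90 effect is:

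- q = 10% in both arms: −0.32 days with deaths kept, −0.20 with all deaths dropped
- q = 10% control, 12% intervention: −1.67 with deaths kept, −1.72 with all dropped

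This contrast changes little.

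**Step 4: the DAH-90 effect itself.** As an illustration, suppose the 13% − 11.05% = 1.95% of patients saved all go to care homes, nobody else is discharged away from home, and nothing else changes. Those patients score 0 on DAH-90 whether they die or are saved, so both arms average 64.5 and the true difference is 0. In the destination-recorded set:

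- f = 60%: 64.5 / 0.9337 − 64.5 / 0.922 = 69.08 − 69.96 = −0.9 days
- f = 90%: 64.5 / 0.90055 − 64.5 / 0.883 = 71.62 − 73.05 = −1.4 days

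The selection alone can produce an apparent harm.

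**Step 5: late discharges.** No rule in the plan removes them. A destination can be lost if the patient was discharged after the field closed, or if the record was locked at 60 days. The documents do not say whether closure applied by admission, operation or discharge date.

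**The case against.** The strongest reply is that the text can be read to keep in-hospital deaths. DAH-90 is to be computed like DAOH-90 with one exception, deaths score 0 from registry data, and the primary strategy includes everyone with an available outcome. On that reading a patient who dies in hospital has available data without a destination. This stands as a possible reading. But the stated entry condition is a recorded destination and no sentence restores deaths, so two analysts could produce different results. The protocol cites SAP V4.0, whose separate text is not in the document reviewed; it may settle the point.

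Three further points stand:

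- A reader might infer that the analysis cannot show whether DAOH-90 conclusions extend to DAH-90, or that agreement would be falsely reassuring. The documents do not support this. In-hospital deaths score 0 on both outcomes, the two measures can differ only in patients discharged alive, and step 3 shows the same-patient contrast is nearly unchanged.
- A reader might also infer that late discharges are excluded by design. They are not: a patient randomised well before the field closed and discharged on day 80 would normally have a destination, and the 60-day option serves audit deadlines.
- The analysis is supportive, and section 8.2 acknowledges the data limitation and plans the same-subset comparator.

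**Conclusion.** The point holds in a limited form. As literally written, the subset rule conflicts with the scoring rule beside it and selects patients after randomisation on an outcome component that the trial expects treatment to change.

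Two results are affected. The DAH-90 treatment effect loses the protection of randomisation and, in the illustration, reads −0.9 to −1.4 days when the truth is 0. Comparison (i) sets unlike populations side by side: 3.2 days against about 2.0 to 2.7 days on DAOH-90 alone. Comparison (ii) keeps its value, but only for patients with a known destination.

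These sizes rest on the section 8.1 means and mortality and on an assumed in-hospital share of deaths (50% to 100% for the DAOH-90 range, 60% to 90% for the illustration). The documents give neither that share nor the number of participants with a recorded destination. Loss of late discharges is possible but conditional. The primary and secondary results are unaffected. The change is worth making because it is nearly free and removes a real ambiguity.

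**What to change.** Amend the days-at-home paragraph in section 8.2 and the SAP as follows:

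1. Define the set by a window of randomisation dates in which field 7.9 was in use, whatever happened to the patient afterwards. Choose the end date once it is confirmed whether closure applied by admission, operation or discharge date. If by discharge date, the last eligible randomisation date is 2 September 2019, since 90 days later is 1 December 2019.
2. Score every death within 90 days as 0, and every patient in hospital through day 90 as 0.
3. Treat as missing only patients discharged alive with an unknown or unrecorded destination, including those whose record was locked at 60 days. Bound the result by setting their DAH-90 to their DAOH-90 and then to 0.
4. Run comparison (ii) on this same set.
5. Report the numbers excluded or missing by arm and reason.

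Comparison (i) will still differ by calendar period and should be described that way. The cost is a few sentences and a few lines of code. No new data are needed for deaths or hospital days, which already come from linked records. The downside is that some recruits near the cut-off are lost from a supportive analysis. If SAP V4.0 already specifies this, the protocol wording need only be aligned with it.
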